**Methods:**

The stepped-care DWM/PM + intervention will be tested in a two-arm, parallel-group, randomized controlled trial (RCT) among adult Polish migrant workers with self-reported psychological distress (Kessler Psychological Distress Scale; K10 > 15.9). Participants (*n* = 212) will be randomized into either the intervention group that receives DWM/PM + with psychological first aid (PFA) and care-as-usual (enhanced care-as-usual or eCAU), or into the control group that receives PFA and eCAU-only (1:1 allocation ratio). Baseline, 1-week post-DWM (week 7), 1-week post-PM + (week 13), and follow-up (week 21) self-reported assessments will be conducted. The primary outcome is psychological distress, assessed with the Patient Health Questionnaire Anxiety and Depression Scale (PHQ-ADS). Secondary outcomes are self-reported symptoms of depression, anxiety, posttraumatic stress disorder (PTSD), resilience, quality of life, and cost-effectiveness. In a process evaluation, stakeholders’ views on barriers and facilitators to the implementation of DWM/PM + will be evaluated.

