## Analysis

### Sample size

We aim to detect a small-to-medium Cohen’s *d* effect size of 0.3 on the PHQ-ADS composite score (primary outcome) at the *t*_*4*_ follow-up assessment point, which is based on previous RCTs on PM + [28, 29]. Power calculations suggested a minimum sample size of 74 per group (power = 0.95, α = 0.05, two-sided). With an expected 30% attrition at *t*_*4*_, we aim to include 212 study participants (intervention group: *n* = 106, control group: *n* = 106) over an 18-month inclusion period.

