#### Quantitative data (RCT)

Intention-to-treat (ITT) and per-protocol (PP) analysis will be conducted for both the primary and secondary outcomes. ITT analysis will include all randomized participants (*N* = 212). PP analysis will include participants in the intervention group only if they have (a) clicked through at least three (out of five) modules of the DWM web application, and (b), if they qualified for PM + in terms of K10-distress score at *t*_2,_ attended at least four (out of five) PM + sessions. ITT analysis of the primary outcome will be used to answer the main research question.

To compare differences between the two treatment groups at baseline, t-tests (continuous variables) and chi-squared tests (categorical variables) will be conducted for normally distributed data. For continuous non-normally distributed data, Mann–Whitney tests will be conducted.

To estimate the treatment effect on the primary outcome at *t*_2_, *t*_3_, and *t*_4_, with *t*_4_ being our primary time point of interest, a linear mixed model will be used. This model will have time and treatment as fixed effects (as well as their interaction parameters), a baseline measure of the PHQ-ADS as a covariate, and subjects as random effects. The mean difference between the two treatment groups at each assessment with a 95% confidence interval will be obtained from this mixed model. The same linear mixed model will be used to estimate the effect of the DWM/PM + stepped-care programme on secondary outcomes: symptoms of depression (PHQ-9), anxiety (GAD-7), PTSD (PCL-5), quality of life (EQ-5D-5L), and an outcome-based resilience variable, operationalised as the PHQ-ADS total score against stressor exposure [78].

Missing data will not be imputed but will be treated as missing at random (MAR) as linear mixed models can handle missing data. If some items of a particular scale are missing (i.e. < 50%), the Corrected Item Mean Substitution method will be used [79]. This method uses the item mean across participants of the same study group and time point, weighted by the subject’s mean of completed items. All the above-mentioned analyses will be performed using Jamovi version 2.3.26 [80]. Jamovi is an open-source graphical user interface for R.

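### The primary model, read as written, applies one pooled residual variance and one baseline slope at weeks 7, 13 and 21, so the week-21 standard error can be wrong in either direction

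*Protocol article*

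**What the plan says.** In the protocol article, under Analysis, Quantitative data (RCT), the primary model is set out by its terms. On the fixed part: "This model will have time and treatment as fixed effects (as well as their interaction parameters"). On the rest: "a baseline measure of the PHQ-ADS as a covariate, and subjects as random effects". No residual covariance structure, visit-specific variance, baseline-by-time term or robust standard error is named.

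Inference comes straight from this model: "The mean difference between the two treatment groups at each assessment with a 95% confidence interval will be obtained from this mixed model". Week 21 is singled out in the same section ("being our primary time point of interest, a linear mixed model will be used"). The follow-ups are unevenly spaced ("1-week post-DWM (week 7), 1-week post-PM + (week 13), and follow-up (week 21"). On missing data: "Missing data will not be imputed but will be treated as missing at random (MAR"). The Sample size section expects 30% attrition at week 21 and enrols 106 per arm.

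**The concern.** With a random intercept as the only dependence feature, each follow-up visit has the same residual variance, each pair of visits has the same correlation, and baseline predicts each visit with the same slope. The week-21 confidence interval therefore uses a variance pooled over weeks 7, 13 and 21, with more data coming from the earlier visits.

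That pooling is harmless only if the variance left after baseline adjustment is about the same at all three visits. It need not be. Baseline may predict week 7 better than week 21, or the spread of PHQ-ADS may change over follow-up. If residual variance is higher at week 21 than at the earlier visits, the primary interval is too narrow and the test rejects too often. If it is lower, the interval is too wide and power is lost. Since the primary question is answered at this single visit, the error falls on the main result.

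**Working it through.** **Inputs from the protocol.** 106 per arm, 1:1 allocation, 30% attrition at week 21, and the model terms above. The attrition step reproduces: 74/(1 - 0.30) = 105.7, so 106 per arm. Whether "minimum sample size of 74 per group" follows from the stated effect and power is a separate matter; nothing below depends on it.

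**Assumed inputs, because the documents give none.** Baseline SD 1. Correlation among follow-ups 0.70 for adjacent visits and 0.55 for weeks 7 and 21. Retention 85/78/70% at weeks 7/13/21 (only the 70% is stated), with dropout unrelated to outcome. No treatment effect.

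**Step 1, complete data, by hand.** With SD s_j and baseline correlation r_j at visit j, the variance given baseline is v_j = s_j²(1 - r_j²) and the visit's own slope is c_j = s_j r_j. The model uses one slope b, the mean of the c_j. Its single variance is the average of v_j + (c_j - b)², and its SE is √(2 × variance/106). The true week-21 SE uses v_21 + (c_21 - b)².

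For r = 0.65/0.55/0.45 and constant SD:
- v = 0.5775, 0.6975, 0.7975; b = 0.55; squared slope errors 0.01, 0, 0.01.
- Pooled variance = 0.6908 + 0.0067 = 0.6975; model SE = √(2 × 0.6975/106) = 0.1147.
- Week-21 variance = 0.7975 + 0.01 = 0.8075; true SE = √(2 × 0.8075/106) = 0.1234.
- Ratio 0.929: the SE is 7% too small.

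For r = 0.55 at every visit, all three variances are 0.6975 and the ratio is exactly 1, although the follow-up correlations still decay.

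**Step 2, with dropout.** The random-intercept model was fitted in large-sample form. Its model-based SE was compared with the true (sandwich) SE. Type I error = 2Φ(-1.96 × model SE/true SE).

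| Baseline correlation, wk 7/13/21 | SD, wk 7/13/21 | Model SE | True SE | Ratio | Type I |
|---|---|---|---|---|---|
| 0.65/0.55/0.45 | 1/1/1 | 0.1326 | 0.1447 | 0.917 | 7.2% |
| 0.65/0.55/0.45 | 1/1.05/1.10 | 0.1392 | 0.1585 | 0.879 | 8.5% |
| 0.65/0.55/0.45 | 1/0.95/0.90 | 0.1264 | 0.1312 | 0.964 | 5.9% |
| 0.65/0.55/0.45 | 1/0.925/0.85 | 0.1234 | 0.1245 | 0.991 | 5.2% |
| 0.55 throughout | 1/1/1 | 0.1335 | 0.1347 | 0.991 | 5.2% |
| 0.55 throughout | 1/0.95/0.90 | 0.1275 | 0.1215 | 1.049 | 4.0% |
| 0.55 throughout | 1/0.925/0.85 | 0.1247 | 0.1150 | 1.084 | 3.4% |
| 0.55, follow-ups all 0.70 | 1/1/1 | 0.1325 | 0.1325 | 1.000 | 5.0% |

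**Step 3, cross-checks.** A REML simulation of the first row (4,500 trials) gave a model SE of 0.133 against an empirical 0.148 (10% too small) and 7.2% rejections. Steeper or milder decay at constant SD, with retention 90/80/70%, gave a wider range. Correlation 0.7 per 6 weeks: 0.137 against 0.158 (13% too small), type I error 9.0%. 0.8 per 6 weeks: 0.120 against 0.144 (17%), 10.3%. Mild decay, 0.7 × 0.9 per 6 weeks: 0.132 against 0.141 (6%), 6.6%.

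**The case against.** The strongest reply is that this is a condensed article, and covariance structure, degrees of freedom and a baseline-by-visit term are routine SAP content. The article never says random intercept or compound symmetry, and an SAP could name an unstructured covariance. This stands as a caution: the random-intercept reading is an inference. But the article does not merely name a model family. It lists the fixed terms, the baseline covariate and the random part, and draws the primary interval from that list. A subject random effect with nothing further is most naturally a random intercept.

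The second reply concerns direction, and it stands in full. A reader might infer that week-21 variance is larger, so that the planned test is anti-conservative. The documents do not support that: they report no correlation and no SD by visit. PHQ-ADS is bounded at 0-48 and participants enter above a K10 cut-off, so a falling SD is possible too. With weaker baseline correlations (0.50/0.45/0.40; 0.70 and 0.60 between follow-ups), the SE is 3.5% too small at constant SD and 2% too large if the SD falls 10%.

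A reader might also blame decaying correlation among the follow-up visits. With constant SD and constant baseline correlation, that decay costs nothing with complete data and about 1% with dropout.

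Finally, the stated model is a standard one and, with complete randomised data, unbiased for the week-21 difference. That is right; the point concerns its standard error. How a wrong covariance would affect the estimate when dropout depends on earlier scores was not quantified.

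**Conclusion.** The point holds as a weakness in the stated primary model, not as a demonstrated inflation of type I error. The model's week-21 standard error is right only under a variance pattern that the protocol neither states nor justifies. The main driver is residual variance that differs by visit, through a falling correlation with baseline or a changing SD. Under the main assumptions tabulated, the error runs from 12% too small to 8% too large, with type I error from about 8.5% down to 3.4%. Steeper assumed decay reaches 17% too small; some plausible settings give almost no error. These sizes rest on assumed correlations, SDs and early retention, on the random-intercept reading, and on dropout unrelated to outcome. The change is worth making because it is cheap and removes the dependence on that assumption.

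**What to change.** Specify the primary model as: visit as a factor, treatment x visit, baseline PHQ-ADS x visit, unstructured covariance over the three follow-ups, and REML with Kenward-Roger degrees of freedom. Take the week-21 contrast from it and keep the random-intercept model as a sensitivity analysis. Fit it in R directly if Jamovi cannot. If an SAP already specifies this, the article's description only needs a clarifying note.

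Both parts are needed. In the simulations with 30% attrition, adding baseline x visit but keeping the random intercept left the model SE at 0.874 of the empirical SE (0.7 decay) and 0.836 (0.8 decay).

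The cost is four extra covariance parameters (six instead of two) and two extra slopes, which 212 participants support easily. When compound symmetry holds, the large-sample SE is 0.1325 under both models; in the first row of the table, the unstructured model's SE is 0.1430 against a true 0.1447 for the stated model. No data collection changes. The article reports 138 participants enrolled and no interim analyses, so the change can be recorded before analysis, provided that analysis has not begun since.

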#### Assessments

After screening, data is collected through self-report assessments at four time points: *t*_1_ (baseline, week 1 – sent at the end of screening), *t*_2_ (post-DWM, week 7), *t*_3_ (post-PM + , week 13), and *t*_4_ (follow-up, week 21) with the online programme Castor Electronic Data Capture (EDC) [46]. Each digital assessment with questionnaires will be sent to participants via e-mail and can be completed through any device with Internet access (e.g. smartphone, laptop, tablet). Total completion time of each digital assessment is about 30 min (see ‘Study measures’).

Participants have 14 days to complete the questionnaire When an assessment remains incomplete, participants will receive a maximum of 3 reminders on days 2, 5, and 10 through different communication channels to promote participant retention. Hair samples and (paper) questionnaires are collected at *t*_1_ and *t*_4_ through regular mail. Once the research team receives the hair sample and the hair questionnaire, answers are entered in Castor EDC as well. Participants receive a 10-euro gift voucher for each completed assessment with a maximum of 4 vouchers (*t*_1_-*t*_4_), regardless of whether they send a hair sample.

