#### Primary outcome measure

The primary outcome and endpoint is a combined measure of depression and anxiety at week 21 (*t*_4_, 2-month follow-up) as indicated by the Patient Health Questionnaire Anxiety and Depression Scale (PHQ-ADS). The PHQ-ADS is a validated measure of the combined sum score of the Patient Health Questionnaire depression module (PHQ-9) [55] and Generalized Anxiety Disorder (GAD-7) [56] questionnaire (see secondary outcomes). Answer options for both the PHQ-9 and GAD-7 are ‘not at all’ (0), ‘several days’ (1), ‘more than half the days’ (2), and ‘nearly every day’ (3) with a sum score of 0–48.

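### Read literally, the secondary-outcome models adjust for baseline PHQ-ADS and not for each outcome's own baseline, which costs precision mainly for PCL-5 and EQ-5D-5L

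*Protocol article*

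**What the plan says.** All of the relevant text is in the protocol article, mostly in Data analysis, Quantitative data (RCT).

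- The model is set out for the primary outcome at t2, t3 and t4. It has time, treatment and their interaction as fixed effects, plus "a baseline measure of the PHQ-ADS as a covariate, and subjects as random effects".
- The next step is: "The same linear mixed model will be used to estimate the effect of the DWM/PM + stepped-care programme on secondary outcomes". The outcomes listed are "symptoms of depression (PHQ-9), anxiety (GAD-7), PTSD (PCL-5), quality of life (EQ-5D-5L), and an outcome-based resilience variable".
- Primary outcome measure explains how the covariate is built: "The PHQ-ADS is a validated measure of the combined sum score of the Patient Health Questionnaire depression module (PHQ-9") and the GAD-7.
- Assessments places a baseline among the data collections: "After screening, data is collected through self-report assessments at four time points", of which t1 is the first. Table 1, which would show the measures taken at each visit, is not reproduced in the text available.
- Study measures makes only the K10, the PHQ-ADS and the suicide screening compulsory. Other questionnaires may be skipped in part or whole.
- Missing data are not imputed. The one exception is item substitution when fewer than half of a scale's items are missing.

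A further model with many baseline covariates is described among the exploratory analyses, but it concerns the primary endpoint only.

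**The concern.** For the primary outcome, baseline PHQ-ADS is the outcome's own baseline, which is the usual choice. Carried over unchanged, the same covariate is a different construct for PTSD symptoms and for quality of life. Baseline enters only as a covariate and effects are estimated at t2 to t4, so an outcome's own t1 value has no other route into the model.

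An outcome's own baseline is usually its best single predictor at follow-up. Leaving it out gives wider intervals than the collected data allow. If the arms happen to differ at t1 on PCL-5 or EQ-5D-5L, part of that difference passes into the estimated effect. The wording also leaves two analyses open, with different estimates and intervals, for each secondary outcome.

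**Working it through.** **Plan's own figure.** There is none for the secondary analyses. The sample-size section concerns the primary outcome only ("effect size of 0.3 on the PHQ-ADS composite score (primary outcome") and is used here just for group sizes: 74 per group at t4, and 74 / 0.7 = 105.7, so 106 randomised per group, which agrees with the article.

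**Inputs that must be assumed.** The documents give no correlations. Let r be the correlation of follow-up with the outcome's own baseline, and r0 the correlation of baseline PHQ-ADS with that own baseline. All results are for a standardised outcome at one time point, as an ANCOVA approximation to the mixed model.

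**Step 1: two plain cases.** Residual variance after adjusting for a covariate with correlation c is 1 − c².

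- Own baseline 0.6, PHQ-ADS 0.4: 1 − 0.36 = 0.64 against 1 − 0.16 = 0.84. The ratio is 0.762, so variance is 24% lower. √0.762 = 0.873, so intervals are 13% narrower. 0.84 / 0.64 = 1.31, the equivalent of 31% more participants.
- Own baseline 0.5, PHQ-ADS 0.4: 0.75 against 0.84. The ratio is 0.893, so variance is 11% lower. √0.893 = 0.945, so intervals are about 5.5% narrower.

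**Step 2: by outcome.** Suppose baseline PHQ-ADS predicts follow-up only through the outcome's own baseline. Its correlation with follow-up is then r0·r, and

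SE ratio (PHQ-ADS covariate / own baseline) = √[(1 − (r0·r)²) / (1 − r²)].

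With r from 0.4 to 0.7:

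| Outcome | r0 assumed | SE larger by |
|---|---|---|
| PHQ-9, GAD-7 | 0.90–0.95 | 1–9% |
| Resilience | 0.7–0.8 | 3–22% |
| PCL-5 | 0.5–0.7 | 5–31% |
| EQ-5D-5L | 0.3–0.6 | 6–37% |

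The ends of the PCL-5 row are:

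- r0 = 0.7, r = 0.4: √(0.9216 / 0.84) = 1.047
- r0 = 0.5, r = 0.7: √(0.8775 / 0.51) = 1.312

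**Step 3: chance imbalance.** With 106 per arm, the SE of a standardised baseline difference is √(2/106) = 0.137. A difference above 0.2 SD in either direction therefore has probability about 0.15 for any one outcome. If the own baseline differs by D, the average amount left in the effect after adjusting for PHQ-ADS is r·D·(1 − r0²), so the share removed is r0². For D = 0.2 SD, no adjustment would leave 0.2 × 0.4 to 0.2 × 0.7 = 0.08–0.14 SD. After PHQ-ADS adjustment:

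- PHQ-9, GAD-7: 0.01–0.03 SD left, 81–90% removed
- PCL-5: 0.04–0.11 SD left, 25–49% removed
- EQ-5D-5L: 0.05–0.13 SD left, 9–36% removed

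**Step 4: scale in terms of power.** Take 74 per arm and borrow d = 0.3 for a secondary outcome. Power is 0.45 with no adjustment and 0.51–0.72 with own baseline. With baseline PHQ-ADS it is 0.46–0.55 for PCL-5 and 0.45–0.52 for EQ-5D-5L. (That 74 per group does not give the stated 0.95 power in a plain two-group comparison is a separate matter; nothing here depends on it.)

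**The case against.** The strongest reply is that nothing is wrong except brevity. In the primary model the PHQ-ADS covariate is the outcome's own baseline, so calling the secondary model the same may simply mean the same form with outcome and baseline swapped together. The article condenses a fuller plan, and an unseen SAP may state the swap. This is fair: a reader might infer that the investigators chose to leave own baselines out, and the documents do not show that. What stands is that the article names a particular scale as covariate and never says it changes. An analyst following the text would use PHQ-ADS throughout. This is a stated choice, not a detail left open.

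A reader might also infer that baseline imbalance goes uncorrected or that the secondary results are biased. Neither follows. PHQ-9 and GAD-7 are the two parts of PHQ-ADS, and resilience is derived from the PHQ-ADS score, so the covariate already does much of the work for three of the five outcomes. For PCL-5 and EQ-5D-5L the correction is partial, not absent. Randomisation keeps every estimate unbiased in expectation under either covariate.

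The size is assumed, and the calculation by outcome favours the concern. If baseline PHQ-ADS also predicts follow-up directly, the loss is smaller.

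Finally, PHQ-ADS has a practical advantage: it is compulsory, whereas t1 PCL-5, EQ-5D-5L and stressor items can be skipped. A mixed model drops anyone whose covariate is missing. This objection stands in full, and the fix has to meet it.

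**Conclusion.** The point holds as one of precision and clear wording, limited to secondary outcomes. As written, the text carries baseline PHQ-ADS into every secondary model and gives no place to the outcome's own t1 value. The consequence is material for PCL-5 and EQ-5D-5L, moderate for resilience, and minor for PHQ-9 and GAD-7. The main research question is answered by the primary analysis, which already uses its own baseline.

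Under the plain assumption of correlations of 0.5 to 0.6 with own baseline and 0.4 with baseline PHQ-ADS, the gain from changing is about 11 to 24% in residual variance. The wider ranges by outcome rest on assumed correlations and on PHQ-ADS acting only through the own baseline, so they are closer to upper limits than to expected values. This is a worthwhile improvement, not a threat to the trial's validity.

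**What to change.** Replace the sentence on secondary outcomes with: *the same model form, with the t1 value of the outcome being analysed as the baseline covariate (baseline PHQ-ADS may be kept as an additional covariate)*. For resilience this means the t1 stressor-reactivity score.

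Add a rule that keeps participants with a missing t1 value in the intention-to-treat analysis. Two options are:

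- put t1 in the outcome vector with a baseline mean common to both arms; or
- impute the mean for the baseline covariate only, using the mean over both arms together so that the imputed value does not depend on allocation.

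The second option needs an explicit exception to the article's statement that missing data are not imputed.

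**Cost.** Two sentences, with no new visits or measures, provided Table 1 confirms that these scales are collected at t1. The small downside is that some t1 values will be missing and need the rule. PHQ-9 and GAD-7 should escape this, since their items are the compulsory PHQ-ADS items. If own baselines were always intended, the change only makes the text say so.

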As an exploratory additional analysis, digital markers will be assessed using open-source tools in a Python environment, which is available on GitHub [38, 74]. Digital markers will be assessed using open source tools in a Python environment, which is available on GitHub [38, 74]. Change over time in digital markers will be calculated using repeated measures analysis of variance (ANOVA). A covariate mixed model of the primary endpoint will be conducted by adding relevant covariates at baseline, including gender, age, education, migration and work characteristics (e.g. duration of stay, type of contract), relationship status, living situation, life events, traumatic experiences, COVID-19-related events. An exploratory analysis will also be conducted to see if steroid hormone levels and baseline and between-session change in digital markers are associated with treatment recovery.

To determine the cost-effectiveness of the DWM/PM + stepped-care programme, health economic analysis will be conducted from a healthcare system and societal perspective. This will be conducted by focusing on the incremental cost per quality-adjusted life year (QALY, based on the EQ-5D-5L) and per change in PHQ-ADS composite score at the *t*_*4*_ follow-up assessment point (week 21). To do so, the total cost of the delivery of the intervention and changes in the uptake of health care will be assessed, using the CSRI. Between-group comparison of mean costs will be conducted using appropriate statistical tests, depending on the type and distribution of data. Univariate sensitivity analysis will be conducted using non-parametric bootstrapping to estimate the uncertainty and variability on trial parameters, which will be addressed by constructing cost-effectiveness planes and acceptability curves.

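### The stated ITT set of all 212 randomised is not delivered by a mixed model on t2–t4 without imputation, and the t4 result rests on MAR alone

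*Protocol article*

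**What the plan says.** Four statements under Data analysis, Quantitative data (RCT), bear on this point.

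- The analysis set: "ITT analysis will include all randomized participants", given as N = 212. The ITT analysis of the primary outcome answers the main question.
- The model: a linear mixed model is planned "To estimate the treatment effect on the primary outcome at" t2, t3 and t4, with t4 as the time point of main interest. It includes "a baseline measure of the PHQ-ADS as a covariate, and subjects as random effects".
- The missing-data rule: "Missing data will not be imputed but will be treated as missing at random (MAR) as linear mixed models can handle missing data".
- The one exception, for scales with fewer than half their items missing: "the Corrected Item Mean Substitution method will be used".

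The Sample size section adds: "With an expected 30% attrition at" t4. The Study measures section makes the PHQ-ADS items compulsory for continuing an assessment, while the questionnaires outside the compulsory set may be skipped.

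The health economic analysis follows under the same heading with its own methods: "the total cost of the delivery of the intervention and changes in the uptake of health care will be assessed, using the CSRI". Mean costs are compared with tests chosen to suit the data, and uncertainty is handled by bootstrapping. That paragraph does not mention missing costs or missing EQ-5D-5L values.

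**The concern.** The article states the analysis set, the model and the missing-data rule, and the three do not fit together. A mixed model uses every outcome row that exists, so it copes with a missed visit. It cannot use a person who has no outcome row. With baseline on the right-hand side of the model, anyone with no assessment after t1 is such a person.

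Item substitution does not help. PHQ-ADS items are compulsory within an assessment, so missing primary data will mostly be whole missed assessments.

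Two things are at stake. First, the report would describe as ITT on all randomised an analysis that holds fewer people. Second, the only assumption stated about the missing t4 values is MAR. The outcome is self-reported, and participants are told their group at the end of the Psychological First Aid call. Dropout that depends on unobserved distress, and differs by arm, is therefore plausible, though nothing in the document demonstrates it.

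**Working it through.** **Inputs.** N = 212, 106 per arm (Randomization; Sample size). Attrition at t4 is 30% (Sample size). Outcome visits are t2, t3 and t4, baseline is a covariate, and there is no imputation (Quantitative data (RCT)). The share with no follow-up at all is not given, so it is varied below as an assumption.

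**The plan's own figure.** 74 / (1 − 0.30) = 105.7, rounded up to 106 per group; 2 × 106 = 212. The attrition step reproduces. The 74 does not follow from d = 0.3 with two-sided α = 0.05 and power 0.95: 2 × (1.960 + 1.645)² / 0.3² gives 289 per group. That is a separate matter on which this point does not depend; 0.3 serves below only as the stated target.

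**Who is in the primary model.** Number contributing = 212 − (number with none of t2, t3, t4). Everyone with no follow-up is also missing t4, so under the expected attrition that number is at most 0.30 × 212 = 63.6, about 64.

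| Assumed share with no follow-up | Not in model | In model |
|---|---|---|
| 0% | 0 | 212 |
| 5% | 11 | 201 |
| 10% | 21 | 191 |
| 20% | 42 | 170 |
| 30% (upper bound) | 64 | 148 |

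The stated set is met only in the first row.

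**Illustration.** One data set of 212 was simulated with assumed between-person SD 7 and residual SD 4. Missingness was completely at random: 42 people lacked all follow-up and 22 more lacked only t4.

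- Planned model: 170 people and 148 t4 values; t4 estimate −3.38 (SE 0.87). The 22 missing only t4 stayed in.
- Baseline as an outcome with a common mean: all 212 people; t4 estimate −3.34 (SE 0.85).

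The second model delivers the stated set but hardly moves the estimate. Being one data set with random dropout, it shows who is counted and says nothing about bias when MAR fails.

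**Dependence on MAR at t4.** Assume 30% are missing at t4 in each arm, and that the missing are worse than MAR predicts by δ_I SD (intervention) and δ_C SD (control). The benefit shrinks by 0.30 × (δ_I − δ_C).

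| δ_I | δ_C | Loss of effect (SD) |
|---|---|---|
| 0.5 | 0.5 | 0.30 × 0 = 0 |
| 0.25 | 0 | 0.30 × 0.25 = 0.075 |
| 0.5 | 0 | 0.30 × 0.5 = 0.15 |
| 1.0 | 0 | 0.30 × 1.0 = 0.30 |
| 0 | 0.5 | 0.30 × (−0.5) = −0.15 (effect grows) |

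Only the difference between arms matters. An observed effect equal to the 0.3 target would be reduced to zero at a difference of 0.30 / 0.30 = 1.0 SD. None of the δ values comes from the document.

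**Costs and QALYs.** The stated reason for not imputing is that mixed models handle missing data. The cost and QALY comparison is described without a mixed model. Each follow-up CSRI looks back 2 months, so a missed t3 (week 13) leaves a stretch of cost that t4 (week 21) does not recover. EQ-5D-5L is analysed in the mixed model as a secondary outcome, but a QALY built from it over 21 weeks is a different quantity. The reason given therefore does not reach this analysis.

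**The case against.** The strongest reply has four parts.

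1. The ITT sentence is there to contrast with the per-protocol set: everyone randomised is eligible whatever their adherence. A likelihood-based mixed model under MAR is a standard primary analysis. Omitting people with no follow-up is not biased under MAR given baseline and arm, and modelling baseline as an outcome adds no t4 information. All of this stands, and it limits the consequence. It does not make the statement of N = 212 correct.

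2. Sensitivity analyses to MAR usually belong in a statistical analysis plan, which is not shown. This stands as regards silence. The article, however, states a general rule against imputation, and delta-adjusted or reference-based imputation would contradict it as worded. The rule needs limiting.

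3. A reader might infer that the economic analysis becomes complete-case and that its results come from a self-selected subset. The document does not say so. The no-imputation sentence belongs to the mixed-model text, in a paragraph that closes by assigning the analyses above it to Jamovi. The economic methods come afterwards, and missing costs may be covered in a plan not shown. Only the narrower statement holds: the reason given does not carry over.

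4. A reader might call the trial unblinded. The article calls it single-blind and blinds the research assistants. The accurate description is that participants know their arm and report the outcome themselves. Missing an assessment is also not the same as leaving the programme: assessments are e-mailed with up to three reminders and a voucher for each one completed, with no stated condition on programme completion.

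**Conclusion.** The point holds in this form: the article promises an ITT analysis of all 212 randomised but specifies a model that excludes anyone with none of t2, t3 and t4. The number contributing could be anywhere from 212 down to about 148. The lower end assumes that attrition at t4 is the expected 30% and that everyone lost misses all three follow-ups. The document does not say where in that range the trial will fall.

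The exclusion alone does not bias the estimate under MAR, and changing the model form alone hardly alters it. The more substantial weakness is that the t4 conclusion depends on MAR with no departure allowed for in the article. The 0.15 SD loss, half the 0.3 target, is one point in an assumed range that runs from no loss to the whole target, or to a gain, depending on how the missing differ between arms. It is not a prediction. For costs and QALYs, the conclusion goes no further than that the mixed-model reason does not apply there.

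**What to change.** (a) Put baseline PHQ-ADS in the outcome vector with a mean common to both arms, so that every randomised participant with a baseline score is in the model. Alternatively, restate the set as randomised participants with at least one post-baseline value. Either way, report by arm how many contribute to the model and how many have a t4 value.

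(b) Limit the no-imputation rule to the primary MAR analysis. Prespecify one sensitivity analysis of t4 on all randomised participants: either delta-adjusted imputation over a range set separately in each arm, with a tipping point, or reference-based imputation.

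(c) State that the mixed-model justification does not extend to the cost and QALY comparison. Use multiple imputation by arm combined with the bootstrap there, unless a health economic plan already sets a rule.

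This costs some wording, standard code and a little more analysis work, and the sensitivity result may be less favourable. No data collection changes. The article plans no interim analysis and analyses only after all data are collected, and 138 participants had been enrolled when it was written, so the change can be fixed before any outcome analysis.
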